### Intervention

The GP and the patient will be informed about the treatment that the patient will be given as soon as randomisation has taken place. The GPs participating in the study have been trained by us to give the injection according to a standard procedure: i.e. to use 40 mg triamcenolon acetate combined with lidocaine 1 or 2% in a 5 ml syringe. They are trained to mark the most painful point with a pen or pencil and desinfect the site. The needle is inserted perpendicular to the skin and directed down to the point of maximal tenderness, 1 ml of the substance will be injected at that point, then the needle should be moved to another place in the painful area and the same procedure should be repeated until the syringe is empty. In case of lack of efficacy, or only temporary effect, this procedure may be repeated after a period of 3 weeks up to 3 months

After the injection the GP will fax us a form with details of the injection given, e.g. the volume that is injected, if the injection was painful, or if there was pain relief after injection or direct side effects.

The control group will receive usual care consisting of analgesics as needed; all patients are free to receive additional treatment from a physiotherapist, although this is not advocated by the investigators.

### Questionnaires

The primary outcome measurements will be experienced recovery at 3 months and at 1 year, measured on a 7-point Likert scale (1 = fully recovered till, 7 = worse than ever) and severity of pain during the last week measured with a numeric rating scale (0 = no pain, 10 = worst conceivable pain). Medical consumption of the patient (e.g. medication, visits to the GP or physiotherapist, hospital treatment and diagnostic tests) will be measured as direct cost. The PRODISC questionnaire will be used to measure the cost effectiveness and will measure the indirect costs, expressed in work staff absence and loss of productivity in paid work, or loss of productivity in not-paid work [12]. The WOMAC (Western Ontario and McMaster University Osteoarthritis Index) is recommended by the Osteoarthritis Research Society for use in clinical trials in people with hip osteoarthritis to measure pain and disabilities [13]. The HOOS (hip disability and osteoarthritis outcome score) [14] is developed as an extended version of the WOMAC, to evaluate the whole domain of patient-relevant outcome in young and active patients and is recently validated in the Dutch language [15]. The HOOS consists of 5 subscales; Pain, other Symptoms, Function in daily living (ADL), Function in sport and recreation (Sport/Rec) and hip-related Quality of life (QOL). Both the WOMAC and HOOS will be used in this study. We use the EuroQol (EQ5D) as instrument to measure quality of life [16].

Finally, we ask the patients who received an injection, to report any side effects of the injection. Table 1 shows the timing of measurements.

**Table 1 T1:** Timing of study questionnaires

	baseline	6 weeks	3 months	6 months	9 months	12 months
Severity of pain: VAS (1–10)	x	x	x	x	x	x
Experienced recovery: Likert (1–7)		x	x	x	x	x
HOOS including WOMAC	x	x	x	x	x	x
Prodisq + medical consumption	x		x	x	x	x
EQ 5 D	x		x	x	x	x
Side effects of injection		x	x	x	x	

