This study we will investigate the efficacy and cost effectiveness of local corticosteroid injections in TPS, using a randomised controlled trial design. We also investigate the role of co-morbidity in relation to the efficacy of this local corticosteroid injection.

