### Sample size

The sample size was calculated to detect an increase in recovery rate of 25% in the intervention group after three months of follow-up (45% recovery in the control group versus 70% recovery in the intervention group). With power 0.8 and alpha 0.05 (two-sided tested) and with a dropout rate of 10%, a total number of 75 patients in each group are needed.

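### Side effects are asked only of injected patients and only as effects of the injection, so reported event rates cannot be compared between the randomised arms

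*Protocol article*

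**What the plan says.** The Questionnaires section of the protocol article closes its list of measurements by stating that "we ask the patients who received an injection, to report any side effects of the injection". Table 1 in that section carries a matching row, "Side effects of injection", marked at 6 weeks and at 3, 6 and 9 months, and blank at baseline and 12 months.

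The Intervention section describes one other record of harm. After an injection the GP faxes a form that notes, among other details, "if the injection was painful, or if there was pain relief after injection or direct side effects". The same section allows a further injection: "this procedure may be repeated after a period of 3 weeks up to 3 months".

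For the comparator the Intervention section says that "The control group will receive usual care consisting of analgesics as needed". The article describes no side-effect item for that treatment.

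The aim at the end of the Background is that the study "will investigate the efficacy and cost effectiveness of local corticosteroid injections in TPS", with the role of co-morbidity as a further question. The Data analyses section plans no comparison of safety.

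**The concern.** Both arms receive a treatment that can have side effects, but patients are asked about them only if they were injected, and only about effects of the injection. The patient knows the treatment and has to decide whether an event was caused by it. Some of the events reported would have happened anyway, and no control rate is available to subtract.

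The item is also tied to receipt of an injection, not to allocation. A patient allocated to injection who never had one would not be asked, while a usual-care patient who was injected would be. The resulting groups are not the randomised groups, although the Abstract states the intention-to-treat principle for primary and secondary outcomes.

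At stake is what the report can say about tolerability beside the efficacy result. This matters most if the treatments turn out similar. In that case the Data analyses section falls back on cost minimisation, and a reader choosing between the two would want to know how they compare on side effects.

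**Working it through.** The point is about data collection, so the main check sets the statements side by side. The arithmetic only gives a sense of scale.

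**1. Who is asked, and about what**

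| Source of information on harm | Patients covered | Content | Follow-up times |
|---|---|---|---|
| Patient item (Questionnaires, Table 1) | Those who received an injection | Side effects of the injection | 6 weeks; 3, 6, 9 months |
| GP form (Intervention) | Those who received an injection | Pain, relief, direct side effects | After the injection |
| Medical consumption (Table 1) | No limit to one arm stated | "medication, visits to the GP or physiotherapist, hospital treatment and diagnostic tests" | 3, 6, 9, 12 months |
| EQ5D (Table 1) | No limit to one arm stated | Quality of life | 3, 6, 9, 12 months |

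The first two rows name harm but have no control counterpart. The last two cover both arms but do not label anything as harm. No row gives an event rate that can be set against the same rate in the other arm.

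**2. The 12-month column**

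Table 1 has six rows. Five are marked at 12 months: pain, recovery, HOOS with WOMAC, Prodisq with medical consumption, and EQ5D. Only the side-effect row is blank. A questionnaire is therefore due at that time in any case, and months 9 to 12 go unasked. With repeat injections allowed up to 3 months, the 6- and 9-month items still follow that window.

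**3. The plan's own sample size, for reference**

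Inputs from the Sample size section: "45% recovery in the control group versus 70% recovery in the intervention group", power 0.8, two-sided alpha 0.05, dropout 10%.

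- Pooled formula: n = [1.96·√(2·0.575·0.425) + 0.8416·√(0.45·0.55 + 0.70·0.30)]² / 0.25² = 60.2, so 61 per group.
- With continuity correction: (60.2/4)·[1 + √(1 + 4/(60.2·0.25))]² = 67.95, so 68 per group.
- With dropout: 68/0.9 = 75.6, so 76; or 68·1.1 = 74.8, so 75.

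The stated 75 per group is reproduced. It is not disputed here and does not bear on the point beyond fixing the arm size.

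**4. What the missing comparator hides**

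The documents give no side-effect rates, so these are assumptions. Take 20% reporting an event after injection and an unmeasured control rate from 5% to 20%:

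- lower end of the excess: 20% − 20% = 0 points
- upper end of the excess: 20% − 5% = 15 points

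**5. What a symmetric question could show with 75 per arm**

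Differences detectable with 80% power (two-sided 0.05, pooled test without continuity correction, no dropout, control rates assumed):

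| Control rate | Detectable rate in the injection arm |
|---|---|
| 2% | 14.5% |
| 5% | about 20% |
| 10% | about 28% |
| 20% | about 41% |

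At 20% versus 5% the 95% half-width of the difference is 1.96·√[(0.20·0.80 + 0.05·0.95)/75] = 0.103, about 10 points. At 20% versus 20% it is 1.96·√[2·0.20·0.80/75] = 0.128, about 13 points.

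As for what one arm can show alone: with no events in 75 injected patients, the one-sided 95% upper bound is 1 − 0.05^(1/75) = 3.9%.

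**The case against.** The strongest reply is that nothing planned goes wrong. The article sets no safety objective and no safety comparison. An item on side effects of the injection, put to those who had one, is a coherent descriptive item. A condensed article may also leave general adverse-event reporting to the full protocol, which is not shown. This stands to the extent that the point is a limitation of design, not a contradiction or a failed analysis. It does not remove the point, because the article does specify the item, the patients who get it and its schedule, and that specification is asymmetric.

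Three stronger readings are tempting, and the documents do not support them.

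- *The cost-effectiveness comparison is one-sided.* It is not. Its inputs are medical consumption, the productivity questionnaire and EQ5D, scheduled through 12 months with no limit to one arm. The side-effect item is not an input.
- *Harm from analgesics is invisible.* This goes too far. Such harm is unlabelled, but it can partly show in medication, consultations, hospital care and EQ5D.
- *The blank at 12 months prevents the comparison.* The restriction to injected patients does that, and filling in the 12-month cell alone would not cure it. Nor do the documents point to a specific late harm that would be missed.

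It can also be said that the remedy gains little: patients know their treatment, early questionnaires of patients already included would lack the question, and 75 per arm gives low precision. All of this is true, and it limits how the result may be read. An imprecise comparison by arm is still more than no comparison.

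**Conclusion.** The concern holds in a limited form. As described, the trial can report how often injected patients attribute side effects to the injection, but it cannot compare patient-reported event rates between the randomised arms. Side effects of the control treatment are captured at most indirectly. The 9-month stop is a separate, minor gap.

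The documents do not allow the size of the loss to be calculated. Under the assumed rates it is an uncertainty of 0 to 15 points in the excess. Symmetric collection would reach about 80% power only at the 15-point end of that range, and would otherwise give a difference with a 95% half-width of roughly 10 to 13 points.

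The conclusion assumes that the full protocol contains no separate adverse-event question for both arms. If it does, the point falls away apart from the 12-month gap in the injection item. The primary efficacy analysis and the cost-effectiveness analysis are unaffected.

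**What to change.** Add one neutral adverse-event question, identically worded for both arms and without reference to the injection, to every follow-up questionnaire (6 weeks; 3, 6, 9 and 12 months). Keep the injection-specific item as an add-on for those who had one. Report the proportion with any event by randomised arm, with the difference and its 95% confidence interval, and label it as a descriptive comparison.

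The cost is a small amendment to the questionnaires and slightly more burden for patients, with no new visits or staff. By the status given in the Discussion, 90 of 150 patients were already included. The remaining 150 − 90 = 60 could be asked from their first follow-up, and those already included from their next questionnaire. Their earlier waves would be missing, and the report should give the number asked at each time by arm.

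The report should also state that patients knew their treatment, so reporting may differ between arms, and that 75 per arm can reveal only large differences. If the question is not added, the report should present side effects as a description of injected patients only and make no comparative statement about tolerability.

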### Sample size

The sample size was calculated to detect an increase in recovery rate of 25% in the intervention group after three months of follow-up (45% recovery in the control group versus 70% recovery in the intervention group). With power 0.8 and alpha 0.05 (two-sided tested) and with a dropout rate of 10%, a total number of 75 patients in each group are needed.

### Data analyses

Difference between the groups in the primary outcome will be analysed based on the basis of the "intention-to-treat" principle. Differences in continuous outcome measures between the groups will be analysed with linear regression techniques and differences in dichotomous outcomes (recovery dichotomised to totally recovered or almost totally recovered versus slightly recovered and less) will be analysed with logistic regression techniques. Baseline differences between the groups will be assessed and checked whether these influence the outcome of the study. Baseline variables that change the outcome by 10% or more will be regarded as confounders and will therefore be added to the regression models.

Regression models will also be used to study effect modification of comorbidity. A cost-effectiveness analyses will be performed from a social and a patient perspective, looking at differences in direct and indirect health care cost between the two groups.

If the trial does not show a difference in disease parameters (VAS and WOMAC) and quality of life (EuroQol) between the groups, the analysis will be reduced to a cost minimisation analysis. This form of analysis evaluates the efficacy of treatment based solely on direct and indirect costs. If the study does find a positive difference in disease parameters and/or quality of life in the injection group, a cost-effectiveness ratio can be determined.

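### Baseline pain enters the model for a primary outcome only under a data-driven 10% rule, instead of being fixed in advance together with the comorbidity stratum

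*Protocol article*

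**What the plan says.** Pain is one of the two primary outcomes. The Questionnaires section defines it as "severity of pain during the last week measured with a numeric rating scale (0 = no pain, 10 = worst conceivable pain"), and the Abstract names 3 months and 1 year as the primary evaluations. Table 1 carries it as "Severity of pain: VAS (1–10)" and schedules it at baseline and at all five follow-up waves. The two scale labels differ, but that does not affect this point.

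Under Data analyses the article says: "Differences in continuous outcome measures between the groups will be analysed with linear regression techniques". Dichotomised recovery goes to logistic regression, and the primary comparison is by intention to treat. Baseline differences are then to be examined. Any baseline variable whose inclusion alters the outcome by a tenth or more is labelled a confounder and put into the model. I read this as a change in the estimated treatment effect, which is the usual meaning of such a rule.

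The Randomisation section stratifies by comorbidity in four strata. Data analyses uses comorbidity for effect modification but does not fix the stratum as a covariate in the main comparison.

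**The concern.** A change-in-estimate rule asks whether a covariate is confounded with treatment. Under randomisation any baseline imbalance is due to chance, and the main reason to adjust for baseline pain is that it predicts later pain. The rule does not look at that. If baseline pain is well balanced it stays out, however prognostic it is, and the unexplained variance it could have removed stays in the standard error.

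The 10% threshold is also relative to the observed treatment effect. The smaller that effect, the more easily a covariate qualifies. The outcome data therefore help to decide which model is reported for a primary outcome, and the model cannot be known before the data are seen. At stake are prespecification and some efficiency.

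**Working it through.** **Inputs from the article (Sample size):** "45% recovery in the control group versus 70% recovery in the intervention group", "With power 0.8 and alpha 0.05 (two-sided tested"), dropout 10%, and "a total number of 75 patients in each group are needed".

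**Assumed, because the article gives no figure:** correlation ρ between baseline and follow-up pain, mainly 0.3 to 0.6; treatment effect on pain of 0.3 to 0.5 SD.

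**1. The stated sample size.** With mean proportion 0.575, the two-proportion formula gives
n = [1.96·√(2·0.575·0.425) + 0.8416·√(0.45·0.55 + 0.70·0.30)]² / 0.25² = 60.2, so 61 per arm.
The continuity correction gives (60.2/4)·[1 + √(1 + 4/(60.2·0.25))]² = 67.95, so 68 per arm. Allowing for dropout, 68·1.1 = 74.8 (75) or 68/0.9 = 75.6 (76). The stated 75 reproduces. It rests on recovery, so the handling of baseline pain does not alter it. Evaluable patients per arm: 75·0.9 = 67.5.

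**2. What fixed adjustment gains over no adjustment.** The residual variance is multiplied by 1 − ρ²: 0.91, 0.75 and 0.64 for ρ = 0.3, 0.5 and 0.6. The 67.5 per arm then act like 67.5/0.91 = 74.2, 67.5/0.75 = 90.0 and 67.5/0.64 = 105.5. This is an outer bound, because the plan does not rule adjustment out.

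**3. How often the plan's rule brings baseline pain in.** In SD units, adjusted effect = u − b·Δx, where u is the unadjusted effect, Δx the chance imbalance in baseline pain and b ≈ ρ. The covariate enters when |b·Δx| ≥ 0.1·|u|. With 67 per arm, SD(Δx) = √(2/67) = 0.173. For ρ = 0.5 and u = 0.48, entry needs |Δx| ≥ 0.048/0.5 = 0.096, which is 0.56 standard deviations of Δx and has probability about 0.58. Simulation gives 57%, so baseline pain is left out in 43% of trials. Over ρ = 0.3 to 0.7 and effects of 0.3 to 0.5 SD, it enters in 34 to 80% of simulated trials.

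**4. Power under the rule** (simulation, 67 per arm, 0.4 SD effect, two-sided 5%):

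| ρ | never adjusted | 10% rule | always adjusted |
|---|---|---|---|
| 0.3 | about 63% | 65% | 67% |
| 0.5 | about 63% | 72% | 75% |
| 0.6 | about 63% | 78% | 82% |

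Before rounding, a run of 20,000 trials gives losses of 67.2 − 65.7 = 1.5, 75.5 − 72.7 = 2.8 and 81.6 − 77.9 = 3.7 points.

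**5. Where the loss comes from.** At ρ = 0.5 and 0.5 SD, the true spread of the estimate is 0.152 under the rule, 0.150 always adjusted and 0.173 never adjusted. The point estimate is thus almost as precise as with full adjustment, because the rule omits baseline pain mainly when the imbalance is small. In those trials, however, the unadjusted standard error is reported. The average reported standard error is about 2 to 7% too wide.

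**6. Under no effect.** The rule rejects in about 4.2 to 4.7% of trials, slightly conservative against the nominal 5%.

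The simulations use normal outcomes, equal arms, no missing data and baseline pain as the only candidate covariate. Screening many baseline variables was not simulated.

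**The case against.** The strongest reply is that the plan does provide for baseline pain. It is a baseline variable, the rule covers it, and with a plausible correlation it would enter in about half of trials or more, giving an estimate nearly as precise as full adjustment. This is correct and sets the size of the point. A reader might infer that pain is analysed without baseline adjustment and set about 64% power against 68 to 83%. That comparison is between never and always adjusting, and the plan does neither.

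A reader might also infer that the other follow-up waves are ignored, that patients who miss the 3- or 12-month form are dropped, and that bias follows because the trial is open label. The article does not say so. Its wording on linear regression is generic, and it states neither a complete-case analysis nor a method for missing data. A condensed article may leave both to the full protocol or analysis plan. Its only figure is the 10% planned dropout, about 7 to 8 patients per arm, and nothing in it indicates differential non-return.

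It can further be said that linear regression at prespecified time points is valid and that omitting a baseline covariate does not bias a randomised comparison. Both are true. What remains is that the covariate rule is stated outright. An unseen analysis plan would have to replace it, not merely add detail to it.

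**Conclusion.** The point stands as one of prespecification with a small efficiency cost. The stated 10% rule is poorly suited to a randomised comparison because it disregards prognostic strength and makes the model for a primary outcome depend on the result. Against fixed adjustment it costs about 1 to 4 points of power (65 to 78% versus 67 to 82%), and reported standard errors are somewhat too wide when baseline pain is left out. These figures depend on the assumed correlations of 0.3 to 0.6 and the 0.4 SD effect. The documents do not support any claim of bias, inflated type I error, an inadequate sample size or exclusion of patients. The change is worth making because it costs almost nothing, not because the analysis as planned would be invalid.

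**What to change.** Under Data analyses, replace the 10% rule for the main comparisons with covariates fixed in advance:

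- **Linear models (pain, HOOS/WOMAC):** treatment arm, the baseline value of the scale analysed, and the comorbidity stratum used in randomisation.
- **Logistic model for recovery:** treatment arm, baseline pain and the comorbidity stratum. Recovery has no baseline value in Table 1, so baseline pain takes that place.

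Any further baseline adjustment can be kept as a labelled sensitivity analysis. The change should be made before outcomes are compared by arm.

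Optionally, the 3- and 12-month contrasts could be taken from one repeated-measures model over the five collected waves. This is a suggestion and does not correct a stated error.

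The cost is a few lines of wording. Baseline pain, the baseline scales and the stratum are already collected, and the number of patients does not change.

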### Randomisation

After receiving the baseline questionnaire and informed consent, an independent person will randomise each patient based on computerized randomisation lists to either receive the injection therapy or the usual care, consisting of analgesics as needed. This randomisation is stratified for yes or no comorbidity and uses randomisation block sizes of ten, yielding four strata: one lacking comorbidity, one with low back pain, one with osteoarthritis, and one stratum with both.

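### The 10% change rule lets the trial's own results choose the covariates of the primary models; the effect on error rates is modest, and fixing the covariates in advance is a cheap improvement

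*Protocol article*

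**What the plan says.** All references are to the protocol article.

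- **Data analyses, models.** For pain: "Differences in continuous outcome measures between the groups will be analysed with linear regression techniques". Recovery is dichotomised, and differences in it "will be analysed with logistic regression techniques".
- **Data analyses, covariates.** Two sentences govern adjustment. The first is "Baseline differences between the groups will be assessed and checked whether these influence the outcome of the study". The second is "Baseline variables that change the outcome by 10% or more will be regarded as confounders and will therefore be added to the regression models". No covariate is named, and nothing confines the rule to a secondary analysis.
- **Randomisation.** Allocation is by chance: "an independent person will randomise each patient based on computerized randomisation lists". It is stratified by comorbidity, in blocks of ten.
- **Questionnaires, Table 1.** Pain severity is collected at baseline.
- **Sample size.** The planning risks are "45% recovery in the control group versus 70% recovery in the intervention group", with 75 patients per group.

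**The concern.** A change-in-estimate rule is meant for observational data, where a shift in the estimate may show confounding. Under randomisation an imbalance is chance, so there is no systematic confounder to find. The rule instead lets each variable's effect on the estimated treatment difference decide whether it enters the primary model. The model is then unknown until the outcomes are in, and its standard error treats it as if it had been fixed beforehand.

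Two features of the wording add to this.

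- The text speaks of changing the outcome by 10%. The natural reading is a change in the estimated treatment effect, but for recovery that could mean the odds ratio or the log odds ratio.
- The odds ratio is non-collapsible. Adjusting for a prognostic variable moves it away from 1 even when the arms are perfectly balanced, so a shift need not mean confounding.

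At stake are the error rate of the primary tests, the coverage of their intervals, and which odds ratio is reported.

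**Working it through.** **1. Number analysed.** Take p0 = 0.45, p1 = 0.70, mean 0.575, difference 0.25, two-sided alpha 0.05, power 0.80.

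n = [1.960·√(2·0.575·0.425) + 0.842·√(0.45·0.55 + 0.70·0.30)]² / 0.25² ≈ 60.2, so 61 per arm.

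With continuity correction: (60.2/4)·[1 + √(1 + 4/(60.2·0.25))]² ≈ 68 per arm.

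For 10% dropout, 68/0.9 = 75.6 and 68 × 1.1 = 74.8. The stated 75 is reproduced to within one patient. The checks below use 68 per arm.

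**2. The two scales.** The planned odds ratio is (0.70/0.30)/(0.45/0.55) = 2.85, with logarithm 1.048.

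- A 10% change in the log odds ratio is a shift of 0.1 × |estimate|. That is 0.105 at the planned effect and shrinks to zero as the effect does.
- A 10% increase in the odds ratio is a shift of ln 1.1 = 0.095, whatever the effect.

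The two nearly coincide at the planned effect and part company near the null. In null simulations a pure-noise variable was selected in about 35% of trials on the log scale and about 1.6% on the odds-ratio scale. With the prognostic candidates of step 4, at least one was selected in 96–98% of null trials on the log scale and 52–57% on the odds-ratio scale.

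**3. Non-collapsibility alone.** Let Z be standard normal and perfectly balanced, with log odds ratio b per SD. Choose a0 and a1 so that E[expit(a0 + bZ)] = 0.45 and E[expit(a1 + bZ)] = 0.70. The adjusted odds ratio is exp(a1 − a0).

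| Odds ratio of Z per SD | Adjusted odds ratio | Change from 2.85 |
|---|---|---|
| 1.65 | 3.03 | +6.1% |
| 2.0 | 3.18 | +11.6% |
| 2.7 | 3.53 | +23.8% |

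The 10% line is crossed at about 1.90 per SD on the odds-ratio scale and 1.96 on the log scale. A balanced binary covariate needs an odds ratio of about 3.4 to 3.8.

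**4. Type I error, every variable tested.** Candidates are independent standard normal variables. Their number and strength are assumptions, because the article lists none. There were 6,000 null trials per logistic row (Wald test) and 12,000 per linear row. Monte Carlo standard error is about 0.2 to 0.35 points. Figures are rejection rates in %, nominal 5%.

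| Model and candidates | Unadjusted | Rule, log or coefficient scale | Rule, odds-ratio scale | Same covariates, fixed |
|---|---|---|---|---|
| Logistic, 5 at 0.4 log-odds per SD | 5.0 | 6.7 | 6.5 | 5.5 |
| Logistic, 10 at 0.3 | 4.9 | 7.4 | 6.7 | 6.0 |
| Linear, 5 at 0.3 SD | 4.9 | 3.5 | – | 5.2 |
| Linear, 10 at 0.2 SD | 4.6 | 3.5 | – | 4.6 |
| Linear, 5 noise | 4.8 | 5.0 | – | 4.8 |
| Linear, 10 noise | 5.1 | 5.7 | – | 5.2 |

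A second set of 5,000 null logistic trials gave 6.3% and 7.5% on the log scale, against 4.9% and 5.9% with the covariates fixed. On the log scale, selection therefore adds 6.7 − 5.5 = 1.2 to 7.5 − 5.9 = 1.6 points. The rest of the excess over 5% is small-sample inflation of the adjusted Wald test.

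**5. Type I error, screening first.** Suppose only variables that differ between arms reach the 10% check, with a difference flagged at p < 0.20 (an assumed threshold). Logistic type I error was then 3.8–5.0% on the log scale and 4.4–5.6% on the odds-ratio scale. A further set of runs under this reading gave 4.5–5.3%.

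**6. Power.** In the linear model, with 5 candidates at 0.3 SD and a 0.5 SD effect, power was 93.9% under the rule, 97.1% with the same covariates fixed and 83.4% unadjusted. In the logistic model, with 5 candidates at 0.4, it was 78.4% under the rule (log scale) and 77.8% with the covariates fixed.

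**The case against.** The strongest reply is that the two covariate sentences belong together: baseline differences are assessed first, and only variables that differ reach the 10% check. This is a fair reading. On it, a perfectly balanced covariate never reaches the check, and step 5 shows no material inflation for recovery. The wording also permits testing every variable, so the non-collapsibility point and the 6–7% hold only under that condition. Screening does not remove the main fault, since the model still depends on the observed data. The linear model stayed conservative, at about 3%, under either reading.

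Four stronger readings are tempting and not supported.

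- **That the rule nearly always fires when there is no effect.** This is so on the log scale with the assumed candidates. On the odds-ratio scale it is 52–57%, and the article does not fix the scale.
- **That the rule distorts the odds ratio.** With assumed prognostic candidates, the median at 45% against 70% moves from 2.86 to about 3.5 if every variable is tested. This is mostly the ordinary step from a marginal to a conditional odds ratio. In one comparison, fixed adjustment for the same five variables gave 3.92 and the rule 3.6. With screening first, the rule gave 3.04–3.06.
- **That the 5% level fails badly.** At most one to two points are due to selection, and for pain the error is mostly on the conservative side.
- **That the article should have listed its covariates.** Leaving the list to an analysis plan would be no fault. The point is that the article states a selection rule, and an analysis plan that followed it would inherit the problem.

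**Conclusion.** The point holds, at moderate severity. The article sets a data-driven rule for the covariates of the primary models in a randomised trial. It leaves the scale of the 10% undefined, and the usual standard errors ignore the selection.

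The numerical harm is modest. Logistic type I error is about 6–7% if all variables are tested and about 5% if only visibly imbalanced ones are. For pain it is about 3–4% with prognostic candidates, with power about 3 points below fixed adjustment (97.1 − 93.9 = 3.2). These figures assume 68 analysed per arm and 5 to 10 independent candidates of the stated strengths. With five pure-noise candidates the linear model showed no distortion. A balanced covariate can trip the rule by itself only if it is strongly prognostic and every variable is tested.

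The better reason to change the rule is that the primary model should be known before the outcomes are. The planned 75 per group is unaffected.

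**What to change.** 1. Delete the 10% rule for the primary analyses.
2. Fix the covariates of every primary model before outcomes are examined: the comorbidity stratum used in the randomisation and baseline pain severity. If wanted, add one or two further prognostic variables by name.
3. For recovery, report the standardised (marginal) risk difference with its 95% confidence interval beside the adjusted odds ratio. This is the scale of the sample size calculation, and it keeps the change from a marginal to a conditional odds ratio from being read as confounding.
4. Keep any data-driven adjustment as a labelled sensitivity analysis, stating the candidate variables, any screening step and the scale of the 10%.

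The cost is a change of analysis wording. The stratum and baseline pain are already collected, and neither the sample size nor the visit schedule changes. The one downside is that a chance imbalance in an unlisted variable is handled only in the sensitivity analysis.
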